## Abstract

**Background:**

Walking in everyday life requires the ability to adapt walking to the environment. This adaptability is often impaired after stroke, and this might contribute to the increased fall risk after stroke. To improve safe community ambulation, walking adaptability training might be beneficial after stroke. This study is designed to compare the effects of two interventions for improving walking speed and walking adaptability: treadmill-based C-Mill therapy (therapy with augmented reality) and the overground FALLS program (a conventional therapy program). We hypothesize that C-Mill therapy will result in better outcomes than the FALLS program, owing to its expected greater amount of walking practice.

**Methods:**

This is a single-center parallel group randomized controlled trial with pre-intervention, post-intervention, retention, and follow-up tests. Forty persons after stroke (≥3 months) with deficits in walking or balance will be included. Participants will be randomly allocated to either C-Mill therapy or the overground FALLS program for 5 weeks. Both interventions will incorporate practice of walking adaptability and will be matched in terms of frequency, duration, and therapist attention. Walking speed, as determined by the 10 Meter Walking Test, will be the primary outcome measure. Secondary outcome measures will pertain to walking adaptability (10 Meter Walking Test with context or cognitive dual-task and Interactive Walkway assessments). Furthermore, commonly used clinical measures to determine walking ability (Timed Up-and-Go test), walking independence (Functional Ambulation Category), balance (Berg Balance Scale), and balance confidence (Activities-specific Balance Confidence scale) will be used, as well as a complementary set of walking-related assessments. The amount of walking practice (the number of steps taken per session) will be registered using the treadmill’s inbuilt step counter (C-Mill therapy) and video recordings (FALLS program). This process measure will be compared between the two interventions.

**Discussion:**

This study will assess the effects of treadmill-based C-Mill therapy compared with the overground FALLS program and thereby the relative importance of the amount of walking practice as a key aspect of effective intervention programs directed at improving walking speed and walking adaptability after stroke.

**Trial registration:**

Netherlands Trial Register NTR4030. Registered on 11 June 2013, amendment filed on 17 June 2016.

**Electronic supplementary material:**

The online version of this article (doi:10.1186/s13063-016-1527-6) contains supplementary material, which is available to authorized users.

## Background

The ability to adapt walking to environmental circumstances, such as the ability to avoid obstacles and to secure safe foot placement in a cluttered environment, is a prerequisite for safe walking in everyday life circumstances. This gait adaptability or walking adaptability [1, 2] is often reduced after stroke [3, 4], which might contribute to the high fall risk in this population [5]. There is thus a clear need to improve this aspect of walking ability in people with stroke.

One of the most promising exercise therapies that include practice of walking adaptability is task-specific gait training [5]. Task-specific gait training refers to the practice of associating functional tasks with walking. The benefits of task-specific training in stroke rehabilitation have been demonstrated in several studies [6–8]. Besides task-specific training, context-specific training is a well-accepted rehabilitation principle after stroke, suggesting that training should target the goals relevant for the needs of people with stroke attuned to their environmental circumstances [6, 8]. Hence, including walking adaptability exercises in training interventions aimed at improving safe community ambulation seems appropriate and potentially beneficial for people with stroke.

The FALLS program [9] is one such task-specific and context-specific type of overground training intervention, which integrates the practice of complex situations of community walking, such as walking over an obstacle course (Fig. 1a). The FALLS program is based on the Nijmegen Falls Prevention Program, which was designed for community-dwelling older adults with a history of falling, and was shown to reduce the number of falls in this population [10, 11]. Although the effectiveness of the FALLS program needs to be determined in people with stroke, it has been shown to be feasible for this population [9].

**Fig. 1 Fig1:**
[figure not shown]
Snapshots of the two interventions aimed at improving walking speed and walking adaptability: (**a**) obstacle course of the overground FALLS program; (**b**) targeted-stepping exercise of treadmill-based C-Mill therapy

C-Mill therapy is another promising example of task-specific and context-specific training with an emphasis on walking adaptability exercises. The C-Mill (Fig. 1b) is an instrumented treadmill augmented with task-relevant visual context (e.g., obstacles, stepping targets) projected on the treadmill’s surface [12]. This context can be administered in a gait-dependent manner, owing to online monitoring of timing and location of foot placements [13]. The projected obstacles and stepping targets make C-Mill therapy well suited for task-specific and context-specific training because step adjustments are required to adapt to the projected context similar to the step adjustments required to adapt to environmental circumstances during community ambulation. A recent proof-of-concept study showed that C-Mill therapy in the chronic stage after stroke is not only well received by this population, but also beneficial [14]. C-Mill therapy resulted in training-related increments in walking speed and improvements in various other walking-related clinical scores. In addition, the ability to make step adjustments improved (i.e., higher obstacle-avoidance success rates) after 5–6 weeks of C-Mill therapy, and these adjustments required less attention (i.e., reduced dual-task interference), suggesting that the step adjustments evolved in a more automatized manner after a period of C-Mill therapy [15].

Besides task-specific and context-specific training, other key ingredients for effective rehabilitation include variability in practice, feedback of performance, and amount of movement practice [6–8, 16, 17]. Both interventions comprise variability in practice, given their wide variety of tasks and exercises. Moreover, both interventions allow for performance feedback, either by group discussions and direct feedback provided by therapists (FALLS program) or by direct feedback of walking adaptability exercise performance, e.g., visual feedback with regard to obstacle hits (C-Mill therapy). However, treadmill-based C-Mill therapy probably allows for a greater amount of walking practice (defined as the number of steps taken per session), because it incorporates treadmill walking, which has been suggested to elicit more steps per session than overground training [18–22]. In this study, we will empirically test this suggestion, using the amount of walking practice as a process measure.

The study’s aim is to compare the effects of two promising interventions for improving walking speed, walking adaptability, and commonly used clinical measures of walking and balance in persons after stroke: treadmill-based C-Mill therapy [14, 15] and the overground FALLS program [9]. We expect that C-Mill therapy will result in better outcomes than the FALLS program because of the expected greater amount of walking practice per session of equal duration.

## Methods

### Participants

In total, 40 persons who had a stroke will be recruited from the inpatient and outpatient population of rehabilitation center Reade (Amsterdam, The Netherlands) to participate in this study. Inclusion criteria are first-ever stroke ≥3 months ago, walking or balance deficits confirmed by a physician, clinical diagnosis of hemiparesis, age ≥18 years, general walking ability as indicated by a Functional Ambulation Category score ≥3 [23], and the ability to understand and execute simple instructions. Exclusion criteria are orthopedic and other neurological disorders that affect walking (e.g., Parkinson’s disease), other treatments that could influence the effects of the interventions (e.g., recent Botulin toxin treatment of the lower extremity), contra-indication to physical activity (e.g., heart failure, severe osteoporosis), moderate or severe cognitive impairments as indicated by a Mini-Mental State Examination [24] score below 21, or severe uncorrected visual deficits. Persons with stroke who are eligible for participation will be informed about the study by their rehabilitation specialist, both orally and in writing. All participants will provide a written informed consent.

### Study design

The proposed study is a single-center, parallel group randomized controlled trial with pre-intervention, post-intervention, retention, and follow-up tests to determine the relative efficacy of the interventions: treadmill-based C-Mill therapy and the overground FALLS program. After giving informed consent, participants will be randomly assigned to one of the two interventions using an automated, custom-made minimization algorithm written in MATLAB. The minimization procedure is based on time after stroke, age and Functional Ambulation Category score to balance groups for these stratification factors. The research assistant will enter the data for randomization in the algorithm and the participant will subsequently be informed about the resulting group allocation before the pre-intervention tests. Subsequently, the assessor will schedule the participants for the assigned 5 week intervention program. Pre-intervention tests (T0) to characterize groups and obtain baseline values of primary and secondary outcome measures will be performed one week prior to the intervention program. Within one week after completing the intervention, post-intervention tests (T1) will be performed. The same tests will be conducted 5 weeks (retention tests, T2) and 12 months (follow-up tests, T3) after completing the intervention. All assessments will be performed at the rehabilitation center. Because of the nature of the intervention studied, therapists and participants cannot be blinded to group allocation. The assessor will also not be blinded to group allocation, because of pragmatic constraints related to the planning of assessments and therapy sessions. Figure 2 shows a flow chart of the procedures that participants will undergo at T0, T1, T2 and T3.

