### Data analysis

Descriptive group statistics will be used to characterize the two intervention groups in terms of sex, age, height, body mass, Mini-Mental State Examination, Functional Ambulation Category, medication use, co-morbidities, side and location of the lesion, current living situation, daily functioning and the use of assistive devices, as well as perceived discomforts during and after therapy sessions and participant’s experience with the therapy. An independent *t* test will be used to compare the mean number of steps taken per session between the two interventions.

Primary and secondary longitudinal outcome measures that are normally distributed will be analyzed using repeated-measures ANOVA with the between-subject factor group (two levels: C-Mill therapy and the FALLS program) and the within-subject factor time (four levels: pre-intervention [T0], post-intervention [T1], retention [T2], and follow-up [T3] tests). Post-hoc analysis using independent *t* tests between groups per time level will be performed in case of significant interaction effects. For ordinal or non-normal distributed variables, we will use Mann–Whitney *U* tests and Friedman tests to evaluate possible main effects of group and time, respectively. To analyze possible interactions between groups and times, we will apply Kruskal–Wallis tests to change scores (i.e., relative to the previous time level) at T1, T2, and T3. When significant, Mann–Whitney *U* post-hoc tests will be performed to identify between-group differences in change scores per time level. Significant effects are assumed for *P* < 0.05. Data will be analyzed as randomized. Missing data will be imputed using the data from the last available measurement.

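### The three minimization factors are covariates in none of the planned tests, so the between-group comparisons are conservative to the extent that these factors predict the outcome

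*Protocol article*

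**What the plan says.** The protocol article, under Study design, states that "participants will be randomly assigned to one of the two interventions using an automated, custom-made minimization algorithm written in MATLAB". It goes on to name three balancing factors: "The minimization procedure is based on time after stroke, age and Functional Ambulation Category score to balance groups for these stratification factors". Functional Ambulation Category is shortened to FAC below.

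Under Data analysis, normally distributed outcomes "will be analyzed using repeated-measures ANOVA with the between-subject factor group (two levels: C-Mill therapy and the FALLS program"). The only other term in that model is "the within-subject factor time (four levels: pre-intervention [T0], post-intervention [T1], retention [T2], and follow-up [T3] tests"). The follow-up step is also fixed: "Post-hoc analysis using independent *t* tests between groups per time level will be performed in case of significant interaction effects". For the other outcomes: "For ordinal or non-normal distributed variables, we will use Mann–Whitney *U* tests and Friedman tests to evaluate possible main effects of group and time, respectively". For interactions among those outcomes, "we will apply Kruskal–Wallis tests to change scores (i.e., relative to the previous time level) at T1, T2, and T3", followed by Mann–Whitney tests on change scores where significant.

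None of the three factors is a covariate or stratum in any of these tests. Age and FAC appear in the descriptive statistics, and FAC is itself a secondary outcome. The Sample size section bases the trial on the independent t test, with a difference of 0.50 km/h, an SD of 0.47 km/h and no allowance for covariates.

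**The concern.** Minimization makes the two arms alike on three factors that were chosen because they are thought to matter. That lowers the true variability of the difference between arms. A test that leaves the factors out does not see this: their variance stays in its error term, and it reports the standard error that simple randomization would have produced. Confidence intervals are then wider than the design warrants, and the test rejects less often than its nominal 5%.

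Some association is likely here, since FAC grades walking ability and the primary outcome is walking speed. What is at stake is precision in a trial of 20 per arm. The factors must be known for every participant in order to allocate, so using them needs no new data.

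**Working it through.** **1. The plan's own figure.** Inputs from Sample size: Δ = 0.50 km/h, SD = 0.47 km/h, two-sided α = 0.05, power 80%.

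n = 2 × 0.47² × (1.960 + 0.842)² / 0.50² = 13.87, rounded up to 14 per group. This reproduces. Dropout of 10% gives 14/0.90 = 15.6, so 16; 25% gives 14/0.75 = 18.7, so 19. The planned 20 covers both. Exact t-test power without covariates is 0.773 at 14, 0.803 at 15 (20 less 25%) and 0.906 at 20 per group.

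**2. Why the unadjusted test is conservative.** Its standard error is SD × √(2/n) = 0.47 × √(2/20) = 0.149. If the factors explain a share R² of the variance and the arms are balanced on them, the true SD of the estimate is close to 0.149 × √(1 − R²). At R² = 0.3 that is 0.149 × 0.837 = 0.124. The test then in effect demands 1.96/0.837 = 2.34 true standard errors, which corresponds to a type I error near 1.9% under perfect balance.

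**3. Simulation, because minimization does not balance perfectly.** Assumptions not in the article: three binary factors with equal effects, a biased coin of 0.9, and R² from 0 to 0.5. There were 40 participants and 3,000 runs per setting (Monte Carlo standard error about 0.4 points at 5%). The comparison is at T1, without T0. The 0.30 km/h difference is illustrative; 0.50 km/h is the plan's value.

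| R² | Reported SE, unadjusted | True SD of estimate | Type I error, unadjusted t | Power at 0.30 km/h, unadjusted / adjusted | Power at 0.50 km/h, unadjusted / adjusted | Type I error, group × time F |
|---|---|---|---|---|---|---|
| 0 | 0.147 | 0.147 | 5.3% | 48% / 48% | 91% / 90% | 5.2% |
| 0.1 | 0.148 | 0.142 | 4.5% | 51% / 55% | 92% / 93% | 4.3% |
| 0.3 | 0.148 | 0.127 | 2.1% | 49% / 64% | 93% / 97% | 5.3% |
| 0.5 | 0.149 | 0.111 | 0.8% | 50% / 80% | 96% / 99.7% | 5.1% |

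As a contrast, random allocation to two arms of 20 without minimization, at R² = 0.3, gives a reported SE of 0.148, a true SD of 0.148 and a type I error of 5.1%. The conservatism comes from balancing on the factors and then leaving them out.

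**4. The interaction test.** It is a within-person test. A factor that shifts all four of a participant's measurements by the same amount disappears once the person's mean is subtracted. Adding such effects left the F statistic unchanged in every run, as the last column reflects. The same cancellation covers the tests on change scores. It fails only if a factor predicts change over time.

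**5. Cost of adjusting.** Exact t-test power at the plan's 0.50 km/h, with residual SD 0.47 × √(1 − R²) and 3 degrees of freedom lost:

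| Per group | Unadjusted | R² = 0 | 0.1 | 0.2 | 0.3 | 0.5 |
|---|---|---|---|---|---|---|
| 15 | 0.803 | 0.800 | 0.839 | 0.879 | 0.917 | 0.977 |
| 20 | 0.906 | 0.905 | 0.932 | 0.955 | 0.974 | 0.996 |

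The T0 value is in none of these models. T0 walking speed would absorb part of what the factors predict, so their further gain on top of it would be smaller.

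**The case against.** The strongest reply is that the test that comes first is not affected. The group-by-time interaction decides whether the t tests are run at all, and time-constant effects of age, time after stroke and FAC cancel from it. That stands, and it confines the point to the between-group tests. It is not absolute: entry starts at three months after stroke with no upper limit and follow-up runs to 12 months, so time after stroke could plausibly predict change. The article gives no figure for this, and it was not simulated.

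Second, R² is not stated and could be small. FAC is restricted to 3–5 at entry, which narrows one factor. This also stands: at R² = 0.1 the effect is minor, and at zero there is none.

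Third, a reader might infer that the trial is underpowered or has lost power it was promised. The article does not support this. Its 14 per group rests on an unadjusted SD and claims nothing from balancing, and the unadjusted t test keeps about 0.80 power at 15 per group.

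Fourth, it might be said that covariates belong in a separate analysis plan. That does not answer the point, because the article names its models and tests explicitly and they contain only group and time.

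**Conclusion.** The point holds for the ANOVA group main effect, the independent t tests per time level (the tests that size the trial) and single-time Mann–Whitney tests. The figures were computed for the t test; the direction carries over to the other two. Across assumed R² values of 0, 0.1, 0.3 and 0.5, the t test's true type I error is about 5%, 4.5%, 2% and 1%. At the plan's 0.50 km/h and 20 per group, adjustment changes power from 0.906 to between 0.905 and 0.996.

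It would be wrong to conclude that every planned analysis has inflated standard errors: the interaction and change-score tests do not, unless the factors predict change. Nor is there a risk of extra false positives, since the error is conservative. It would also be too much to say that the factors are used nowhere, because FAC is analysed as an outcome and age and FAC are described; they are absent as covariates.

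The size rests on the assumed R², the simplified minimization scheme, and 0.47 km/h being the SD of the quantity that the t test compares. This is an inexpensive gain in precision, not a flaw that invalidates the design.

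**What to change.** For normally distributed outcomes, replace the unadjusted t tests at T1, T2 and T3 with between-group comparisons that include time after stroke, age, baseline FAC and the T0 value of the outcome as covariates. ANCOVA at each time or a covariate-adjusted repeated-measures model would do. State how each factor is coded. If the factors are left out, say why.

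The factors cost 3 degrees of freedom, or 4 if FAC is entered as a three-level category; the T0 value takes one more. If the factors are not prognostic, power falls only from 0.803 to 0.800 at 15 per group. No new data or extra participants are needed.

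The Mann–Whitney, Friedman and Kruskal–Wallis tests take no covariates. They may stay as they are, or be replaced by a covariate-adjusted ordinal model, which would be a larger rewrite of that paragraph.

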### Outcome measures

After group allocation, pre-intervention tests will be performed to assess the baseline values of primary and secondary outcome measures and to collect participant characteristics (sex, age, height, body mass, medication use, co-morbidities, side and location of the lesion, current living situation, daily functioning and the use of assistive devices). The primary outcome measure in this study will be walking speed. Walking speed will be assessed using the 10 Meter Walking Test [33], which has been shown to be a reliable and robust means for measuring walking speed [34].

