A methodological strength of this study is that both interventions will be matched for therapy duration, frequency, and therapist attention. This means that if there is a superior effect on walking adaptability and walking speed of one of the interventions, this will be realized by the same investment in time and resources. Furthermore, both interventions implicitly utilize and train the direct visuolocomotor control of walking in an enriched environmental context [52, 53], allowing for a direct and natural visuolocomotor control in which the point of gaze is typically coupled to future foot placement locations. The two interventions in this study are similar with regard to visuolocomotor control of step adjustments relative to environmental context (e.g., real obstacles in the FALLS program, real visual obstacles in C-Mill therapy). The proposed trial of Hollands *et al.* [54] also testifies to the growing interest in the use of visual cues for task-specific gait training, thereby also implicitly training visuolocomotor control [54]. Hollands *et al.* intend to compare usual care without visual cues to overground visual cue training and treadmill visual cue training (using the C-Mill) in persons with stroke to examine the feasibility of task-specific locomotor practice incorporating visual cues. Therefore, our study, in combination with the study of Hollands *et al.* [54], might underpin the importance of visuolocomotor control in gait rehabilitation, as well as the potential surplus value of a treadmill in that regard.

A limitation of this study is that it involves only one center. This might influence the generalizability of the research results to other rehabilitation centers. Another limitation of this study is the non-blinding of the assessors. To reduce potential influence of this limitation on the outcomes, instructions will be standardized and tasks will be computerized when possible.

In summary, this study will shed light on the effects of treadmill-based C-Mill therapy compared with the overground FALLS program and thereby on the relative importance of the amount of walking practice as an important ingredient of effective interventions of walking speed and walking adaptability after stroke. Hence, the results of this study will be important in optimizing effective intervention programs directed at improving walking speed and walking adaptability after stroke.

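### Baseline (T0) is measured after participant and assessor know the allocated arm, so an arm-dependent shift at T0 that does not last to T1 would bias the group-by-time interaction and the T0-to-T1 change

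*Protocol article*

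**What the plan says.** Methods, Study design, gives the sequence. After consent, the research assistant enters the data into the minimization algorithm, and "the participant will subsequently be informed about the resulting group allocation before the pre-intervention tests". Next, "the assessor will schedule the participants for the assigned 5 week intervention program". T0 takes place one week before that programme. Its role is stated there too: "Pre-intervention tests (T0) to characterize groups and obtain baseline values of primary and secondary outcome measures".

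Methods, Outcome measures, repeats the order: "After group allocation, pre-intervention tests will be performed to assess the baseline values of primary and secondary outcome measures".

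On blinding, Study design says that "therapists and participants cannot be blinded to group allocation" because of the nature of the intervention. It continues: "The assessor will also not be blinded to group allocation, because of pragmatic constraints related to the planning of assessments and therapy sessions". Neither statement sets T0 apart from the later visits.

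The Discussion names the unblinded assessor as a limitation and offers this mitigation: "instructions will be standardized and tasks will be computerized when possible". It does not mention that baseline follows disclosure of the arm.

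**The concern.** A baseline taken before anyone knows the arm can differ between groups only by chance. One taken after disclosure can also differ because of the disclosure. Several outcomes here are open to that. The 10 Meter Walking Test (primary) and the Timed Up-and-Go depend on effort. The Activities-specific Balance Confidence scale, the Walking Questionnaire and the activities-of-daily-living scale are reported by the participant. The investigators also state that they expect C-Mill therapy to do better, and the assessor who measures T0 knows the arm.

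T0 matters in the planned analysis (Methods, Data analysis). It is one of the four levels of the time factor, so it enters the group-by-time interaction, and that interaction decides whether the post-hoc tests are done. It is the reference for the T1 change score in the rank-based branch. Because missing values are filled with the last available measurement, a T0 value can also be carried into later visits.

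The other reason to raise it is that it looks avoidable. Participants cannot be blinded once therapy starts, but that does not explain telling them before T0. The reason given for the assessor is planning, which does not require that the assessor do the booking.

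**Working it through.** **1. Is any T0 result needed for allocation?** The minimization uses time after stroke, age and Functional Ambulation Category. The first two are background data, and the third is already needed for the inclusion criterion (score of at least 3). So no T0 result is needed, and nothing in the minimization requires disclosure before T0.

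**2. Does the assessor know the arm at T0?** The assessor books the assigned programme, T0 is timed one week before that programme, and the blinding statement makes no exception for T0. Read together, yes.

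**3. How a shift at T0 would act.** Let τ be the true difference between arms in the T0-to-T1 change. Let d0 and d1 be the differences between arms (C-Mill minus FALLS) at T0 and T1 that come only from knowing the arm.

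- Planned order: expected contrast = τ + d1 − d0, so the bias is d1 − d0.
- T0 before disclosure: expected contrast = τ + d1, so the bias is d1.

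If d1 = d0, the planned contrast is unbiased. If d1 = 0, the bias is −d0. Only the part of the T0 shift that does not persist to T1 does harm in the planned order.

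**4. Where T0 enters.**

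- Repeated-measures ANOVA: T0 is a level of time, so it is part of the interaction.
- Rank-based branch: only the T1 change uses T0. Changes are taken from the preceding visit, so the T2 change uses T1 and the T3 change uses T2.
- Post-hoc t tests at each visit: those at T1 to T3 contain no baseline, except for participants whose T0 value has been carried forward.

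**5. The plan's own figure.** Inputs from Methods, Sample size: Δ = 0.50 km/h, SD = 0.47 km/h, two-sided α = 0.05, power 80%.

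N = 2 × 0.47² × (1.960 + 0.842)² / 0.50² = 13.87, rounded up to 14 per group. This agrees with the article. Allowing for dropout, 14/0.90 gives 16 and 14/0.75 gives 19, so 20 covers the stated 10–25%.

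**6. Illustration of size.** The documents give no shift, so b = |d0 − d1| is assumed over a range. It is also assumed that 0.47 km/h is the SD of the change. The test is a two-sample t test on the T0-to-T1 change. At 20 per group the standard error is 0.47 × √(2/20) = 0.149 km/h, with 38 degrees of freedom. Rejection probabilities come from the noncentral t distribution with noncentrality b/0.149 (no true effect) or (0.50 − b)/0.149 (true effect 0.50 km/h, shift working against it).

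| Net shift b, km/h (m/s) | b/Δ | Type I error, 20 per group | Power, 20 per group | Type I error, 15 per group |
|---|---|---|---|---|
| 0 | 0% | 5.0% | 90.6% | 5.0% |
| 0.05 (0.014) | 10% | 6.2% | 83.9% | 5.9% |
| 0.10 (0.028) | 20% | 10.1% | 74.6% | 8.7% |
| 0.15 (0.042) | 30% | 16.6% | 63.1% | 13.5% |
| 0.20 (0.056) | 40% | 25.9% | 50.3% | 20.3% |
| 0.25 (0.069) | 50% | 37.4% | 37.4% | 29.0% |

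Fifteen per group is 20 less 25% dropout. The rows refer to the net shift: a T0 shift of 0.20 km/h of which half persists to T1 belongs in the 0.10 row. The table is for the T0-to-T1 contrast, not for the four-level interaction test, which would also need the correlations between visits.

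**The case against.** The strongest objection is about persistence. Participants and assessor know the arm at every visit. An awareness effect that stays constant cancels in the T0-to-T1 change under the planned order, whereas with T0 before disclosure the same effect would enter that change in full. By the algebra above, if more than half of the T0 shift persists, the absolute bias in this one contrast is smaller under the planned order. This stands. It is why the claim is confined to a shift that does not persist, and why no net direction is given. It does not defend the order, though: relying on two unmeasured effects to cancel is not a safeguard. The open-label effect at T1 cannot be avoided and is already in the per-visit comparisons. The effect at T0 can be avoided.

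The second objection is logistic. C-Mill therapy runs in pairs and FALLS in groups of four to six, and T0 is tied to the start of the programme, so the arm may have to be known early to set dates. This also stands, and it argues against running the minimization only after T0. It does not require that participant or assessor be told early.

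Third, the Discussion already concedes the unblinded assessor and gives mitigation. That covers part of the problem. It does not address the participant's own knowledge at T0, or the order of steps.

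Some stronger readings are tempting but not supported:

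- A reader might infer that baseline is in fact shifted, or shifted in favour of C-Mill. The documents show only that it can be.
- A reader might infer that every change and comparison is affected. The rank-based T2 and T3 changes and the T1 to T3 t tests do not use T0, apart from carried-forward values.
- A reader might argue that a baseline-adjusted model is compromised. None is planned.
- A reader might infer that people who withdraw on hearing their arm defeat the analysis as randomized. The article describes no such withdrawals, and that phrase can mean analysis by assigned arm.

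**Conclusion.** The concern holds in a limited form. The article states twice that baseline follows allocation, states once that the participant is told the arm before T0, and leaves the assessor unblinded throughout. An arm-dependent shift at T0 that does not last to T1 would bias the group-by-time interaction and the T0-to-T1 change. The risk falls mainly on the effort-dependent and self-reported measures, including the primary outcome.

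The order of steps is certain. The existence, direction and size of any bias are not, and cannot be derived from the documents. The illustrative figures (type I error about 6% at a net shift of 0.05 km/h and 10% at 0.10 km/h, with 20 per group) rest on an assumed shift and on taking 0.47 km/h as the SD of change. The order should be changed because the risk is avoidable at little cost. It does not by itself invalidate the trial.

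**What to change.** For all further participants:

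1. The minimization may still be run early so that pairs and groups can be planned.
2. The research assistant who runs the algorithm holds the result and books both the therapy slot and the T0 date. Until T0 is done, the booking shown to participant and assessor should not reveal the programme.
3. The arm is disclosed to participant and assessor only when T0 is complete.

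In the report, give the number of participants whose T0 followed disclosure, and state this as a limitation beside the unblinded assessor. A sensitivity analysis that leaves those participants out is not recommended. Recruitment began in 2013 and results are expected in 2017, so few of the 40 might remain.

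Cost: booking moves from the assessor to another existing role, which assumes that the two roles are held by different people (the article names them separately but does not say so). Participants learn their programme only in the week before it starts. The sample size stays at 14 per group before dropout and 20 after. The change does not remove open-label influence at T1 to T3.
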